# Improving GHB withdrawal with baclofen: study protocol for a feasibility study for a randomised controlled trial

**DOI:** 10.1186/s13063-016-1593-9

**Published:** 2016-09-27

**Keywords:** GHB, Gamma-hydroxybutyrate, GBL, Gamma-butyrolactone, GHB/GBL withdrawal, Baclofen, Benzodiazepine, GABA_B_, GHB/GBL dependence

## Abstract

**Background:**

GHB (gamma-hydroxybutyrate) and its pro-drugs GBL (gamma-butyrolactone) and 1,4-butanediol (1,4-BD) are central nervous system depressants whose street names include ‘G’ and ‘liquid ecstasy’. They are used recreationally predominately for their stimulant and pro-sexual effects or for sedation to help with sleep and/or to ‘come down’ after using stimulant recreational drugs. Although overall population prevalence is low (0.1 %), in some groups such as men who have sex with men, GHB/GBL use may reach 20 %. GHB/GBL dependence may be associated with severe withdrawal with individuals presenting either acutely to emergency departments or to addiction services for support. Benzodiazepines are currently prescribed for GHB/GBL detoxification but do not prevent all complications, such as behavioural disinhibition, that may require hospitalisation or admission to a high dependency/intensive care unit. The GABA_B_ receptor mediates most effects of GHB/GBL and the GABA_B_ agonist, baclofen, has shown promise as an adjunct to benzodiazepines in reducing withdrawal severity when prescribed both during withdrawal and as a 2-day ‘preload’ prior to detoxification. The key aim of this feasibility study is provide information about recruitment and characteristics of the proposed outcome measure (symptom severity, complications including delirium and treatment escalation) to inform an application for a definitive randomised placebo controlled trial to determine the role of baclofen in the management of GHB/GBL withdrawal and whether starting baclofen 2 days earlier improves outcomes further.

**Methods/design:**

This is a prospective, randomised, double-blind, placebo-controlled feasibility study that will recruit participants (aged over 18 years) who are GHB/GBL-dependent and wish to undergo planned GHB/GBL detoxification or are at risk of acute withdrawal and are inpatients requiring unplanned withdrawal. We aim to recruit 88 participants: 28 unplanned inpatients and 60 planned outpatients.

During detoxification we will compare baclofen 10 mg three times a day with placebo as an adjunct to the usual benzodiazepine regimen. In the planned outpatient arm, we will also compare a 2-day preload of baclofen 10 mg three times a day with placebo. Ratings of GHB/GBL withdrawal, sleep, depression, anxiety as well as GHB/GBL use will be collected. The main data analyses will be descriptive about recruitment and characterising the impact of adding baclofen to the usual benzodiazepine regimen on measures and outcomes of GHB/GBL withdrawal to provide estimates of variability and effect size. A qualitative approach will evaluate research participant and clinician acceptability and data collected to inform cost-effectiveness.

**Discussion:**

This feasibility study will inform a randomised controlled trial to establish whether adding baclofen to a benzodiazepine regimen reduces the severity and complications of GHB/GBL withdrawal.

**Trial registration:**

ISRCTN59911189. Registered 14 October 2015. Protocol: v3.1, 1 February 2016

## Background

### GHB/GBL use and dependence

GHB (gamma-hydroxybutyrate) and its related analogues GBL (gamma-butyrolactone) and 1,4-butanediol (1,4-BD) are central nervous system depressants and their street names include ‘G’ and ‘liquid ecstasy’ [1, 2]. GBL and 1,4-BD are converted to GHB after ingestion and, therefore, all three drugs have similar pharmacological actions and profiles [1, 2]. There is limited use of 1,4-BD in the UK and, therefore, hereafter we will use the term GHB/GBL to refer to these compounds. They are used recreationally predominately for their stimulant and pro-sexual effects, although some individuals use them for their sedative effects and/or to help ‘come down’ after using stimulant recreational drugs [3–5]. Although overall population prevalence of use is low, the Crime Survey for England and Wales reported that use significantly rose from 0.0 % in 2010/11 to 0.1 % in 2011/12; subsequent surveys did not collect GHB/GBL data [6]. However, the use of these drugs is more common in a number of subpopulation groups. In particular, in populations such as clubbers and men who have sex with men (MSM), lifetime prevalence of GHB/GBL use ranges from 3.9 to 14.3 %, with last-month prevalence of use of up to 4.6 % [7]. Almost a quarter of those surveyed in ‘gay-friendly’ South London dance clubs in July 2011 reported GHB/GBL use that night, second to mephedrone at 41 % [8]. Similarly, attendees at two London sexual health clinics (December 2013 to March 2104) reported lifetime prevalence of use of GHB at 19 % and GBL at 13 % [9].

Reports from the UK’s Advisory Council on Misuse of Drugs [10] and European Monitoring Centre for Drugs and Drug Addiction (EMCDDA) [7] have highlighted the potential for both significant acute toxicity and also dependence associated with GHB/GBL. The latest data from Public Health England reports that the numbers of people presenting to treatment services with problems with GHB/GBL continue to rise from 18 (2 % of new presentations involving ‘club drugs’ (methamphetamine, mephedrone, ketamine, ecstasy, and GHB/GBL)) of those seeking treatment in 2005–2006 to 249 (5 %) in 2013–2014 [11] and the number of deaths implicating GHB are also rising from none in 1993 to 12–20/year in 2008–2012 [12]. Our clinical experience is consistent with this. Presentations with acute GHB/GBL toxicity to the emergency department (ED) and Clinical Toxicology Service (one of the sites in this study) at Guy’s and St. Thomas’s Hospital Foundation Trust (GSTT) increased from 158 in 2006 to 270 in 2010 [13]; and there has been an increase in the numbers of individuals seeking help from services such as Antidote (supporting the lesbian, gay, bisexual and transgender (LGBT) community) and the Club Drug Clinic, Central North West London NHS Foundation Trust (CNWL) for GHB-related problems. Antidote has seen an increase in GHB-related problems from 1.7 % (*n* = 3) of total referrals in 2005 to 57 % (*n* = 317) in 2010 and 44 % (*n* = 334) in 2013–2014.

GHB/GBL use is associated with a risk of physical dependence and a potentially life-threatening withdrawal syndrome, unlike other club drugs such as stimulants which do not have a pronounced withdrawal syndrome [14]. Therefore, a disproportionate number of GHB/GBL-dependent users compared with other club drug users require help for a potentially life-threatening withdrawal syndrome. Management of GHB/GBL withdrawal or detoxification can present challenges to clinicians and dependent users due to the rapidity of onset of the withdrawal and the severe clinical features that can occur. Regular use of GHB/GBL (typically multiple times per day every day over a period of at least a few months) can lead to dependence with dependent users typically using the drug every 1–4 h to prevent the onset of withdrawal [15–18]. Withdrawal symptoms occur typically within hours following last use due to GHB/GBL’s rapid elimination (T_1/2_ is approximately 27 min) and may also occur during recovery from acute intoxication (overdose) [2, 11, 18, 19]. A proportion of the patients with GHB dependence may, therefore, use alcohol or other drugs such as benzodiazepines, ‘Z drugs’ (e.g. zopiclone) and/or baclofen to self-manage withdrawal symptoms, insomnia and cravings. Typically these are used to help increase the time between dosing overnight to enable them to sleep. The clinical features of GHB withdrawal are similar to alcohol withdrawal but often with more rapid onset. GHB withdrawal can also resemble acute stimulant toxicity and coingestion of other drugs. Identification of GHB dependence and withdrawal can be complicated by a lack of awareness by nonspecialist centres, particularly in emergency cases [20].

### GHB/GBL withdrawal and its treatment

GHB/GBL withdrawal has many similar features to alcohol withdrawal, including tremor, sweating, anxiety, agitation and confusion; however, it is generally more severe, has a more rapid onset and more prominent neuropsychiatric features such as delirium and psychosis [2, 15, 18]. In common with alcohol withdrawal, benzodiazepines have been the pharmacotherapeutic mainstay for GHB/GBL withdrawal [18]. However, our clinical experience suggests that using benzodiazepines alone may be insufficient, with up to 50 % of individuals presenting to our ED and initially 4 % of those in our outpatient clinic requiring acute medical care [21, 22]. This latter group had either developed significant delirium and/or worsening of their initial acute delirium on presentation that required escalation of treatment, including admission to intensive care and use of additional sedatives (e.g. barbiturates or propofol) with the associated intubation and mechanical ventilation for airway support as described [15]. Acute delirium, agitation and/or psychosis results in further risks to the individual, as well as to the staff treating them due to the severity of their agitation and violent behaviour. There has been one death reported as a ‘complication of GHB/GBL withdrawal’. The individual in this case was treated with benzodiazepines for 12 days, developed pneumonia and suffered a cardiac arrest and we feel that the significance of the GHB dependency/withdrawal in the death is unclear and it is likely that the death is not directly related to dependence/withdrawal [23]. Despite the severity of GHB/GBL withdrawal and concerns about how to best manage unplanned and planned detoxification, at this time there is no systematic evidence base on which to base a nationally or internationally agreed treatment protocol. One review produced an algorithm based on the amount of use and the presence of delirium [24]. For those with severe dependence (more than three doses of GHB/GBL per 24 h or over 30 g GHB or/over 15 g GBL) and ‘medical complications’, admission for detoxification and supportive medical care with high-dose diazepam (150–200 mg/24 h) was suggested. Pentobarbital (barbiturate) in the intensive care unit (ICU) was suggested for treating those presenting with delirium. However, it was not clear how long to use pentobarbital for or what to do in those who do not respond to this treatment escalation. For those without delirium, diazepam reducing from 80 to 150 mg per day over 7 days whilst an inpatient was proposed. For those using less GHB/GBL, outpatient management with diazepam reducing from 20 to 40 mg per day over 7 days was suggested. Given the complexity, rapidity of onset of symptoms and complications of withdrawal, such as acute severe delirium, it is important that daily outpatient supervision of GHB/GBL withdrawal occurs in a setting in which admission to an acute hospital is possible should complications arise [25].

Various other pharmacological approaches have been investigated. One trial compared lorazepam and pentobarbital in inpatients for GHB/GBL withdrawal; however, this was not completed due to the inability to recruit sufficient GHB-dependent individuals [26]. Whilst pentobarbital is safe to use in hospital, due to the potential risk of coma and lethal toxicity it is not appropriate for use in community/outpatient detoxification. A Dutch pilot uncontrolled study reported that a reducing regimen of GHB/GBL successfully treated withdrawal and prevented complications, such as delirium, in 23 GHB/GBL-dependent inpatients [27]. GHB in the pharmaceutical preparation sodium oxybate is licensed in the UK for the treatment of narcolepsy associated with cataplexy in specialist sleep services. Current UK prescribing, storage and administration controls (due to the legal status of GHB under the UK Misuse of Drugs Act, 1971) are likely to be practical considerations that limit its usefulness in managing GHB/GBL withdrawal (due to delays in treatment administration). Antipsychotic agents may lower the seizure threshold increasing the risk of GHB withdrawal-related seizures. However, they may also interact with GHB’s effects on the dopaminergic system increasing the risk of neuroleptic malignant syndrome [17, 28].

In summary, a reducing regimen of benzodiazepines alone for GHB/GBL withdrawal is currently considered ‘standard’ treatment and as such is the current ‘best practice’; although in a significant proportion of individuals benzodiazepines alone may be insufficient. The limited research almost always suggests benzodiazepines as the core treatment, with a range of other options having been suggested as helpful of which baclofen has strong pharmacological validity (see next section).

### GHB/GBL withdrawal and the GABA_B_ system

In addition to its activity at endogenous GHB receptors GHB acts at GABA_B_ receptors, which play a key role in withdrawal since GABA_B_ antagonists precipitate withdrawal in GHB-dependent nonhuman primates [1, 29] and can block GHB-induced respiratory depression [30]. Benzodiazepines work through GABA_A_ receptors; however, GHB has limited activity at these receptors, likely explaining their apparently incomplete clinical effectiveness in acute GHB withdrawal. The GABA_B_ agonist baclofen has, therefore, been used on an unlicensed named-patient basis as an adjunct to benzodiazepines to manage GHB/GBL withdrawal by the authors and others [18, 31]. Baclofen is currently only licensed in the UK for the management of muscle spasticity in multiple sclerosis and other conditions.

An uncontrolled case series in 19 GHB/GBL-dependent patients, all of whom except for 2 underwent outpatient treatment, reported that baclofen (10 mg three times a day) in addition to high-dose diazepam during the initial 4–5 days of GHB/GBL detoxification, resulted in no transfers to ICU and several patients commented that baclofen was helpful [18]. Furthermore, the experience of clinical toxicologists and addiction specialists in the UK, including those involved in this study, has been that baclofen is helpful in reducing the complications from GHB/GBL withdrawal. Consequently, the recent update of the British Association for Psychopharmacology’s addiction guidelines [25] suggested using baclofen (10 mg three times a day) as an adjunct to benzodiazepines for GHB/GBL withdrawal.

Furthermore, our clinical experience of GHB/GBL withdrawal in outpatient settings has been that patients who slowly reduce their GHB/GBL use describe significant anxiety and cravings during the few days before commencing medically assisted detoxification. For some, this acted as a deterrent to attending for treatment and a trigger for using higher doses of GHB/GBL. Consequently, we have initially used baclofen 2 days prior to stopping GHB/GBL in a small number of patients. There was very positive feedback from patients regarding the benefit, particularly in terms of reduced cravings and helping to stabilise pre-detoxification GHB use. The use of baclofen in our outpatient clinical service prior to initiating medically assisted detoxification has now become more widespread. The 2 days of pre-detoxification ‘preloading’ of baclofen at a standard dose of 10 mg three times a day has not resulted in any clinical incidents in relation to baclofen. This preloading with baclofen has previously not been formally studied to determine the usefulness of baclofen itself, neither has whether some of the reported benefits relate more to engagement with drug treatment services pre-detoxification than to baclofen itself.

Baclofen has been licensed in the UK for many years for the treatment of spasticity (maximum, 100 mg per day) and can be safely prescribed to a wide range of patients (see Summary of Product Characteristics (SPC), https://www.medicines.org.uk/emc/medicine/23850). Our clinical experience is that it is associated with few side effects. Whilst a withdrawal state is recognised for baclofen, this is unlikely to occur with its use in acute GHB withdrawal due to the short duration (7 to 10 days) of baclofen use in this indication. We suggest that the risk of complications from baclofen withdrawal is considerably less than that of inadequately managed GHB/GBL withdrawal [15, 18]. Nevertheless, whilst the use of baclofen holds promise, there are potential adverse effects on cardiovascular, neurological and respiratory systems so controlled data is urgently required to determine its efficacy and safety in GHB/GBL withdrawal. Optimising outpatient treatment to reduce the risk of complications and hospital admission is important since many individuals decline admission [17, 25]. Despite this complexity and its impact on, and cost to, the individual and the NHS, there is limited knowledge about how to best treat people in planned or unplanned GHB/GBL withdrawal.

### Primary and secondary objectives

The primary objective of this study is to investigate the feasibility of recruiting GHB/GBL-dependent patients and to characterise the impact of adding baclofen to a standard benzodiazepine regimen for the management of GHB/GBL withdrawal in both outpatient (community) and inpatient general hospital settings.

There are several other secondary objectives. These are to examine:Withdrawal symptoms and complications, such as delirium and the requirement for treatment escalation, during detoxification in two populations: those presenting to an ED requiring immediate acute withdrawal management (unplanned) and those presenting to a specialist outpatient Club Drug Clinic requiring GHB/GBL detoxification (planned)Whether, as part of a planned detoxification, starting baclofen 2 days prior to stopping GHB/GBL confers additional benefits in our proposed primary outcome measures (symptom severity, complications such as delirium and requirement for treatment escalation)Recruitment rate monitoring and manage any difficultiesThe impact of GHB/GBL withdrawal on secondary outcome measures (anxiety, depression, sleep, quality of life)The impact of study participation on GHB/GBL use up to 1 month post randomisation and other alcohol/drug useThe views of the research participants and staff about the acceptability of the study designPreliminary information gathered regarding costs of GHB/GBL withdrawal and its management to develop a full economic analysis in a definitive trial

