Any complications arising during preload or detoxification will be recorded. These will be classified as adverse events if they are not one of the following predetermined events which are known to occur in acute GHB/GBL withdrawal or detoxification: agitation or aggression, hallucinations (visual, auditory and/or tactile), tachycardia, seizures, ataxia, sedation, tremor and/or sweating. All adverse events occurring from the time a participant signs the Consent Form until completion of the last study-related procedure will be recorded in the Case Report Form. Any serious adverse event which occurs in a participant will be reported immediately to the chief investigator (CI) and sponsor and, if stated orally, will be followed by a detailed written report.

On day 30 after the start of detoxification (benzodiazepine detoxification, not preload), the researcher will contact the research participant to obtain information about any subsequent use of GHB/GBL, other recreational drugs/novel psychoactive substances/alcohol as well as any medication (prescribed or otherwise obtained) taken and psychosocial treatment/support received for their GHB/GBL dependence. In addition, any issues or events that could be related to their detoxification will be recorded.

Patients will be asked to return any remaining study medication to the clinic so that a pill count can be performed to assess compliance.

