Due to its use in particular communities, specific addiction services have evolved with expertise in managing GHB/GBL withdrawal. Similarly, presentations to EDs vary depending on local clubs and nightlife, since individuals who frequent these tend to also live in the local area. The two services in this study have such local communities and have developed their services to meet the local needs. They are, therefore, well-placed to conduct this study due to their experience and the regular presentations of those with GHB/GBL withdrawal. There is local support and much user interest in this study.

In order to determine whether baclofen is a useful adjunct and to meet thresholds required by national guidelines, e.g. NICE, a trial is still required; without such a trial the use of baclofen will remain based on anecdotal evidence. We are not aware of any other trial using baclofen in GHB withdrawal nor has any other pharmacological approach been shown to be robustly effective or appropriate for community-based detoxification. Importantly this trial also seeks to establish whether the use of baclofen prior to starting detoxification, i.e. a preload improves symptom control and reduces complications during GHB detoxification. This is a novel aspect of the study and addresses a critical question.

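### The stated outcome window for complications and treatment escalation (detoxification) does not match the recording window (preload or detoxification) or the start of randomised treatment in the planned group

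*Protocol article*

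**What the plan says.** All references are to the protocol article.

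- **Randomisation.** Planned participants are allocated after consent and baseline, before preload, to one of three groups: placebo preload then placebo, placebo preload then baclofen, or baclofen preload then baclofen. Study medication in detoxification lasts up to 10 days. The abstract presents preload as a randomised comparison: "we will also compare a 2-day preload of baclofen 10 mg three times a day with placebo".
- **Primary and secondary objectives.** The general objective, for planned and unplanned patients together, is "Withdrawal symptoms and complications, such as delirium and the requirement for treatment escalation, during detoxification in two populations". The preload question is the next, separate objective: whether "starting baclofen 2 days prior to stopping GHB/GBL confers additional benefits in our proposed primary outcome measures". It names symptom severity, complications and escalation, and gives no time window.
- **Discussion.** The preload question is restated as whether "a preload improves symptom control and reduces complications during GHB detoxification".
- **Assessment and outcome measures.** "Any complications arising during preload or detoxification will be recorded". The section then says that complications become adverse events only if they are not on a predetermined list, which includes seizures, ataxia and sedation. It adds: "All adverse events occurring from the time a participant signs the Consent Form until completion of the last study-related procedure will be recorded". Day 30 is counted from benzodiazepine detoxification and expressly not from preload.
- **Data analysis.** Complications and escalation are named as proposed primary outcomes without a window. Adverse events are to be described by arm at an interim analysis. Five escalations in any one group suspend recruitment.

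**The concern.** The randomised treatment period, the recording window and the stated outcome window should agree, or the plan should say why they do not. Here the only outcome window that is stated opens after preload has ended. The preload comparison is where this matters, because the placebo-then-baclofen and baclofen-then-baclofen groups are assigned the same regimen once detoxification begins.

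Preload is also not a neutral run-in. By the preload objective, baclofen is started while GHB/GBL is still being used. The Background reports the clinic's own practice in the same terms ("we have initially used baclofen 2 days prior to stopping GHB/GBL") and names cardiovascular, neurological and respiratory effects as reasons for wanting controlled data. If the preload groups are compared on detoxification days alone, a benefit of preload that appears in detoxification is counted and a complication or admission during preload is not. A participant admitted or lost during preload may also contribute no detoxification outcome, which sits badly with the intention-to-treat analysis intended in the section on discontinuation.

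The study exists to characterise these proposed primary outcomes for a definitive trial, so a badly placed window could be carried forward.

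**Working it through.** The article states no figure to reproduce here, so the check is mainly a comparison of texts.

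**1. Does detoxification include preload in the article's usage?** Mostly not. The Assessment section lists the two as alternatives ("Any complications arising during preload or detoxification will be recorded") and separates them again for the day-30 anchor. The Randomisation section places preload before detoxification proper. On the other side, the preload objective calls starting baclofen early part of a planned detoxification. Usage is somewhat loose, but where times are being fixed the two phases are distinct.

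**2. Windows side by side, planned group**

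| Provision | Section | Window |
|---|---|---|
| Randomised study medication | Randomisation | From preload |
| Complications recorded | Assessment | Preload and detoxification |
| Adverse events recorded | Assessment | Consent to last study procedure |
| General complications and escalation objective | Objectives | Detoxification |
| Preload objective | Objectives | None stated |
| Preload question restated | Discussion | Detoxification |
| Proposed primary outcomes, escalation trigger, interim adverse events | Data analysis | None stated |

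**3. Three events on a preload day, followed through these provisions**

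- *Admission to the general hospital.* It counts towards the five-escalation trigger as worded. It falls outside the detoxification window of the general objective and the Discussion.
- *Sedation, ataxia or a seizure without admission.* It is recorded, and Table 1 has an ad hoc row for expected events. Being on the predetermined list, it is not an adverse event, so it is absent from the interim count by arm. It is also outside the detoxification window. It therefore enters neither comparison.
- *A complication not on the list.* It is recorded, classed as an adverse event and counted by arm. It is outside the detoxification window.

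**4. Share of treatment time.** With preload of 2 days and detoxification of d days, the share is 2/(2 + d).

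- d = 10 (the stated maximum): 2/12 = 16.7%.
- d = 7 (assumed): 2/9 = 22.2%.

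For the contrast between the two groups given baclofen in detoxification, those 2 days are the whole of the difference in assigned treatment. These are shares of time and say nothing about risk.

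**5. Size of any bias.** The article gives no event rate for preload days and does not state how the 60 planned participants divide among the three groups. The 4% outpatient figure in the Background comes from a sentence about benzodiazepines alone, whereas the comparator for preload is placebo preload followed by baclofen. Any calculation would rest wholly on assumed rates, so none is offered.

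**The case against.** The strongest reply is that the operative sections do not exclude preload. The sentence with the detoxification window is the general objective, which also covers unplanned inpatients who have no preload. The preload objective has no window, and neither do the proposed primary outcomes in Data analysis. The Discussion is explanatory prose and defines no endpoint. Complications in preload are recorded, adverse events are collected from consent, and a preload-day admission counts towards the recruitment trigger as worded. The Background reports no baclofen-related clinical incidents with preload. The study is descriptive, and exact windows may be set in the full protocol or analysis plan.

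Much of this stands. A reader might infer that preload is credited with benefit and never charged with harm. The documents do not support that: harm in preload is recorded and reaches safety monitoring, apart from the predetermined events in the adverse event count.

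What the reply does not remove is the mismatch. The general objective names the planned group and gives a window. The preload objective uses the same measures, and the only place that attaches a window to it, the Discussion, uses detoxification. Recording an event does not place it in an outcome comparison. The absence of incidents is uncontrolled experience. Nor is this a detail merely left to another document, because a window is stated and it differs from the recording window.

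**Conclusion.** The point holds as an inconsistency of windows with a possible, unquantified bias in the preload comparison. The general objective and the Discussion state a window that opens after preload, while the Assessment section records from preload and randomised treatment begins there. Read with the Discussion, the preload comparison would omit preload-day complications and admissions. Preload sedation, ataxia and seizures would in addition be missing from the adverse event count by arm.

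This rests on two readings: that detoxification excludes preload, as the Assessment section's usage indicates, and that the Discussion expresses how the preload question will be judged. If the full protocol already counts from the first preload dose, only the article's wording needs correcting.

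Two stronger conclusions should not be drawn. The documents do not show that preload harm is hidden from safety review, and they do not show that preload causes harm. In a descriptive feasibility study this is a moderate point, worth correcting because the correction is nearly free and the outcomes are meant for the definitive trial.

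**What to change.** - In the planned group, count complications and treatment escalation from the first preload dose to the end of detoxification, by randomised arm, in all randomised participants.
- Include the predetermined events in that count, so that preload sedation, ataxia and seizures appear by arm even though they are not classed as adverse events.
- Tabulate the preload and detoxification phases separately beside the combined figure, so that an effect confined to detoxification remains visible.
- Reword the general objective and the Discussion's preload question to agree with the Assessment section, and state the window in the preload objective.

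The cost is wording and one more split in the tables. The article already requires complications in preload to be recorded, so no new data are needed. The one small downside is that the preload result may look slightly less favourable than it would on detoxification days alone.
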